##### Secondary outcomes

Secondary outcomes include self care and quality of life, which will be assessed through well-validated scales, described below and in Table 
2.

*Self-care behavior* will be assessed with the Summary of Diabetes Self-Care Activities Measure – Revised. Reliability and validity for this instrument have been reported to be fair, with a test-retest correlation of 0.40 and internal consistency of 0.47
[38,39].

*Diabetes-specific quality of life* will be assessed with the Diabetes Distress Scale which has been found to have high internal reliability with a Cronbach’s alpha of 0.93, good convergent validity with the Center for Epidemiological Studies Depression Scale (CESD) (r = 0.56) and self-care behaviors including lower adherence to eating recommendations (r = 0.30, p < 0.001) and lower levels of physical activity (r = 0.13, p < 0.01)
[40]. In addition, diabetes distress has been demonstrated to be associated with HbA1c (r = 0.17-0.31, *P =* .00-.001), diet (r = −0.38, *P =* .00), physical activity (r = −0.13, *P =* .01) and medication adherence (r = −0.16, *P =* .00)
[41,42].

These patient-based outcomes were selected because they are direct and relevant measures of knowledge use by patients. Diabetes self-care is a direct measure of knowledge use, and self-efficacy was chosen in order to better understand the mediating variables of knowledge use. Quality of life was chosen as a more holistic and patient-centered measure of impact of knowledge use.

HbA1c, systolic and diastolic blood pressure, LDL-C and weight to be collected every 3 months; these outcomes were chosen to help inform sample size calculations of future prospective trials.

##### Data collection

Data on outcomes will be collected by patient-completed questionnaires; patients will be compensated with a small honorarium for each questionnaire. For the pre-implementation phase, aggregates of patient data will be obtained every three weeks for nine months, resulting in 12 data points. The intervention will then be implemented. For the post-implementation phase, aggregates of patient data will be obtained every three weeks for nine months following the intervention, resulting in another 12 data points. HbA1c and LDL-C will be collected from the hospital medical records. Systolic and diastolic blood pressure will be collected by the research coordinator with an Omron Blood Pressure Model (Model no. HEM-907XL) and recorded as the average of 3 readings. Weight will be collected by the research coordinator with a Seca digital scale (Model 707). Web server log analysis will be done to assess frequency and duration of the specific components of the intervention; metrics selected are described in Appendix C. All participants will be asked at the end of the study to disclose whether other web-based interventions were used, and if so, whether they employed text- or image-based didactic materials, interactive technology or behavioral strategies.

##### Sample size calculation

Using a range of correlations from 0.2-0.8, a 0.05 significance level, and a power of 80%, a sample of at most 52 subjects is required to detect a change of 0.5 units in self-efficacy score before the intervention as compared to after. A formula for paired mean comparisons was used
[43] and the longitudinal nature of the study will only increase the power
[44]. The sample size was further adjusted to account for a 40% expected dropout rate (attrition).

##### Data analysis

Descriptive analysis will examine the distribution of each variable of interest and determine which variables are suitable as covariates for modeling. In addition, exploratory and graphical measures will be used for each of the primary and secondary outcomes to determine the distribution of the outcome of interest to enable a suitable statistical model to be constructed. Should the distribution of the outcome not be ideal, a suitable transformation will be used to enable proper statistical modeling
[45,46]. The primary analysis, assessing the effect of the intervention on self-efficacy, will be examined using a linear mixed model to account for inherent correlation of the repeated measures within each individual
[47]. The model will examine the effect of intervention on the outcome, self-efficacy, while adjusting for the following variables: age, ethnicity, education level, employment status, income (above or below $30 000) and health literacy. Should the data support it the model will also include interactions of these variables with the intervention to determine whether the impact of the intervention on self-efficacy varies for different levels of the variables. Time will also be included in the model to adjust for any trends over time. Model diagnostics will be performed using residual analysis.

Similar modeling will be used for the other outcomes of self-care and quality of life as well as A1C, systolic BP, diastolic BP, LDL and weight. For secondary outcomes, due to the data being collected less frequently, fewer variables will be included in the model. Each model in the secondary analysis will examine the effect of the intervention while adjusting for self-efficacy, income and ethnicity. In addition to these covariates, the outcomes systolic BP, diastolic BP and LDL will also include age as a covariate while the analysis examining weight as the dependent variable will also include insulin use as a covariate. Should the data support it these variables will also be examined as interaction terms with the intervention.

This analysis approach will allow us to examine the effect of the intervention on each of the primary and secondary outcomes while adjusting for other important variables and accounting for the correlation that arises in repeated measures data.

Other variables of interest such as website usage statistics, website user satisfaction and subscales of self-efficacy, self-care and quality of life will be examined using descriptive and graphical analysis.

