Adapt knowledge to local context	In July 2008 the Ontario MOHLTC launched the Ontario Diabetes Strategy, to improve prevention and care for Ontarians with chronic diseases, starting with diabetes, through a mix of prevention, access to technology, personal planning and access to specialized resources and health professionals. All Ontarians with diabetes and their health care providers will be supported through a series of inter-related initiatives. As part of this larger initiative, there is an implementation plan for patient self-management tools, as well as a plan for measuring and reporting on improvements in clinical care and outcomes on a web-based patient portal.
Assess barriers to knowledge use	Barriers to knowledge use can occur at several levels, including the health care system, the health care team and organization, the health care profession, the patient and, finally, the guidelines or their education delivery system. Brown described a similar framework, and categorized barriers to diabetes care on three levels: organization, provider, and patient. Barriers at the patient level include acceptance of the diagnosis, education, self-motivation and adaptation to daily living. Poor adherence to guidelines may be a result of patient preferences, expectations or knowledge. Our initiative will focus on barriers at the patient level.
Select, tailor, implement interventions	(a) Selecting the intervention (Phase 1) Web-based interventions have the potential to bridge the gaps in diabetes care and self-management. Two systematic reviews suggest that web-based media improve knowledge or understanding [9,10], social support [10], behaviour change [10] and clinical outcomes [10] in a variety of disease states. (b) Tailoring the intervention. The intervention will be refined following feasibility (Phase 2) and usability testing (Phase 3) with patients with diabetes. (c) Implementing the intervention. The refined self-management tool (Phase 4) will be implemented in a pilot study (Phase 5).
Monitor knowledge use	A mixed method study, as described in the main text, will be conducted, consisting of an interrupted time series and individual interviews (Phase 5).
Evaluate outcomes	
Sustain knowledge use	Barriers to sustained knowledge use will be addressed in the planning phase of tool development, implementation and dissemination, and further explored upon completion of the pilot study with qualitative methodology (Phase 5).

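### If all patients share the same three-weekly waves and one launch, the primary mixed model omits variation shared within a wave, so its 5% test of self-efficacy is too liberal

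*Protocol article*

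**What the plan says.** All references are to Phase 5 of the protocol article unless noted.

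- **Data collection** describes the pre-launch series and the launch: "aggregates of patient data will be obtained every three weeks for nine months, resulting in 12 data points. The intervention will then be implemented". A second series of 12 three-weekly points follows. No concurrent control and no staggered start are described.
- **Table 1** (Methods) describes the evaluation as a mixed-method study "consisting of an interrupted time series and individual interviews (Phase 5").
- **Data analysis** examines self-efficacy "using a linear mixed model to account for inherent correlation of the repeated measures within each individual". It adjusts for patient characteristics and adds time to take out trends. It presents the approach as dealing with the correlation in repeated-measures data. No term for variation between waves is named.
- **Sample size calculation** gives "a sample of at most 52 subjects is required to detect a change of 0.5 units in self-efficacy score", for correlations from 0.2 to 0.8. It says "A formula for paired mean comparisons was used" and allows for 40% dropout. It gives no SD.
- **Participants** describes a consecutive sample from two family practice units and two endocrinology clinics. No accrual period is given.

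**The concern.** If launch is common, the intervention indicator takes one value for everyone in a wave and switches once. Each wave then contributes one value of the exposure, however many patients answer in it. Self-efficacy scores may move together within a wave, for example because of reminder timing, holidays or clinic events. Such a movement is not reduced by having more patients.

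A patient-level random effect does not absorb it, because it is not constant over a patient's visits. A smooth time trend does not absorb it either, because it is irregular. Entering time as 24 categories is no way out, since the before/after indicator would then be aliased with time. A model that treats different patients' residuals in the same wave as independent therefore reports too small a standard error.

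At stake are the p-value and confidence interval for the primary result: a chance difference between two sets of 12 waves could be read as an effect of the website. This is a variance error. It is present even with no secular trend and no seasonal cycle, and its relative size grows with the number of patients.

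**Working it through.** **Inputs from the article.** 12 + 12 waves (Data collection); N = 52, target change 0.5, correlation ρ from 0.2 to 0.8, significance level 0.05, power 80% (Sample size calculation).

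**Assumptions, not in the article.** Two-sided test; total SD 1; random patient intercepts, so within-patient residual variance is 1 − ρ; linear time; complete data; a shared wave deviation with SD s, independent between waves.

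**1. Reproduce the 52.** For paired means, n = 2·SD²·(1 − ρ)·(1.960 + 0.842)²/0.5². With SD 1 and ρ = 0.2 this is 50.2, so 51 by the normal approximation; the exact t calculation gives 53. Both are close to 52. SD 0.9 or 1.1 gives 41 or 61, so SD 1 is a reasonable reading of the scale on which the trial was sized.

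**2. Variance of the step, common launch.** With an intercept, a linear time term and a step after wave 12, the variance factor for the step over 24 waves is 0.670 (about 2/3).

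- Variance the model reports: 0.670·(1 − ρ)/N
- True variance: 0.670·[(1 − ρ)/N + s²]
- Ratio: R = 1 + N·s²/(1 − ρ)
- Actual type I error: P(|Z| > 1.96/√R)

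Example, ρ = 0.5 and s = 0.10: the model SE is √(0.670·0.5/52) = 0.080 and the true SE is √(0.670·(0.5/52 + 0.01)) = 0.115. R = 1 + 0.52/0.5 = 2.04, and P(|Z| > 1.96/1.428) = 17%.

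| Wave SD s | ρ = 0.2 | ρ = 0.5 | ρ = 0.8 |
|---|---|---|---|
| 0 | 5% | 5% | 5% |
| 0.05 | 7% | 8% | 13% |
| 0.10 | 13% | 17% | 30% |

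A wave SD of 0.10 is one fifth of the target change and about 1% of total variance (0.10² = 0.01 against 1).

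**3. Staggered entry.** Suppose entry is spread evenly over an assumed number of waves, each patient has 12 points before and 12 after an own launch, time runs from own entry, and the shocks stay tied to the calendar. The extra variance becomes s² times the sum, over calendar waves, of the squared total weight that patients place on that wave. Before-launch and after-launch weights now partly cancel. For ρ = 0.5 and s = 0.10:

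| Entry spread over | Type I error |
|---|---|
| 0 waves (simultaneous) | 17% |
| 6 waves | 10% |
| 12 waves (nine months) | 6% |
| 18 waves | 5% |

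**4. After adding a wave effect, common launch.** For complete data the test is equivalent to regressing the 24 wave means on step and trend, with 24 − 3 = 21 df. In 5,000 simulated data sets per setting (N = 52, ρ = 0.5, up to 5% of within-patient residual variance shared within a wave) its type I error was 4.5% to 4.9%. Power for 0.5 units (noncentral t, 21 df) is above 99% at s = 0 for every ρ. At s = 0.10 it is 95%, 99% and above 99% for ρ = 0.2, 0.5 and 0.8.

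**The case against.** **Shared waves are inferred.** A reader might take it as settled that every patient sits on the same 24 waves with one launch date. The article does not say so. Consecutive recruitment commonly means rolling entry, and a common launch after 12 points per patient would need everyone enrolled before the first wave. Elsewhere the study is called a cohort or repeated-measures study, and the interrupted-time-series label appears only in Table 1. This objection stands in part. The aggregated series and the single implementation favour a common launch but do not prove it, and with entry spread over about nine months the inflation nearly disappears at correlation 0.5.

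**The wave variance is unknown.** This stands. At zero the test keeps its 5%. A reader might infer that this trial's error rate is 17% or 30%; the documents support only the direction, given some shared variation.

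**The article may not exclude a wave term.** It states what the mixed model is for and does not list every random effect, and an analysis plan that is not shown could say more. If patient-specific steps with an assumed SD of 0.5 were present and modelled, 0.5²/52 = 0.0048 would be added to both variances (0.0064 and 0.0131 at ρ = 0.5, s = 0.10), and the 17% would fall to about 12%. That reduces the problem without removing it. The article does name one source of correlation and presents the result as adequate, so the point concerns a stated choice.

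**History threats are acknowledged.** Strengths and limitations plans to record secular events, ask about them at exit and examine interaction with time. That helps interpretation but does not alter the standard error.

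**Secondary outcomes.** Because similar modelling is planned for all outcomes, a reader might extend the criticism to HbA1c, blood pressure, LDL-C and weight. These are collected every 3 months and do not sit on the 24 three-weekly waves, so the calculation does not carry over.

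**Conclusion.** The point holds conditionally. If launch and waves are common, as Data collection and Table 1 suggest, and if scores share any random wave-to-wave variation, the model as described understates the standard error of the primary effect. The direction needs no assumed figure beyond those two conditions. The size does: over assumed wave SDs of 0 to 0.10, type I error runs from 5% to between 13% and 30% depending on the correlation, with N = 52 and SD 1. Rolling entry would bring it down, to about 6% at correlation 0.5 and wave SD 0.10 if spread over nine months.

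The documents do not show that the error rate is in fact inflated by a particular amount, and nothing here applies to the 3-monthly clinical measures. It is a cheap and worthwhile improvement to the analysis of self-efficacy and the other three-weekly questionnaire outcomes.

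**What to change.** In Data analysis:

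1. State whether the website is launched on one date for all patients or on a date specific to each patient, and whether the three-weekly points follow the calendar or each patient's entry.
2. Add to the patient-level mixed model a crossed random effect for the calendar three-week period. This works under either launch scheme.
3. Test the intervention term with small-sample degrees of freedom, for example Kenward-Roger (about 21 if launch is common).
4. Use the same term for the other outcomes from the three-weekly questionnaires.

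The cost is one extra random term in the code and a sentence or two of text. No extra data or patients are needed. The confidence interval becomes wider when wave variance is present, as it should. When wave variance is absent almost nothing is lost. With 52 patients and SD 1, power for the 0.5-unit change stays at 95% or more up to a wave SD of 0.10.

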### Phase 1: Intervention development

Our objective was to create an evidence-based, theory-driven self-contained website. Based on our systematic review of electronic tools on topics relevant to diabetes
[13], we selected tools that were known to be effective, relevant and usable. For example, we included multi-media diabetes education modules targeting individuals with low literacy that were demonstrated to be effective in lowering A1c
[16] and that were easy to use
[13]. In addition, we incorporated behavioral intervention strategies that were found to be effective in a systematic review of internet-based interventions, including stress management and communication tools
[17]. For example, we included text- and graphic-based material on coping with diabetes, an online forum to communicate with peers, as well as tips and website-generated reports to facilitate communication with health care providers.

We integrated these interventions with the theoretical framework of self-efficacy, a theory that has not only been validated in predicting and promoting patient behavior change but has also been demonstrated to improve clinical outcomes
[18-25]. For example, diabetes self-management education programs incorporating self-efficacy have been shown in randomized controlled trials to improve knowledge
[25], health behaviour
[24,25], self-efficacy
[23-25], HbA1c
[23-25], and weight
[25] and microvascular complications
[24]. Briefly, self-efficacy refers to “beliefs in one’s capabilities to organize and execute the courses of action required to produce given attainments”
[26]. It arises from one’s successes or failures during previous performances, observations of others’ experiences, verbal persuasion and physiological and affective states, and is mediated by cognitive, motivational, affective and selective processes. We used these sources and mediators of self-efficacy in formatting our site and selecting tools. For example, we incorporated feedback, goal-setting, peer story-telling, and monitoring tools into the website by including computer-generated responses to user entries, a goal-setting application, videos of peer testimonials, trackers for blood glucose, blood pressure, weight and physical activity and a diary) (Figure 
1).

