#### Outcomes

##### Primary outcome

The primary outcome, self efficacy, will be assessed with the Modified Grossman Self-efficacy for Diabetes Scale which has moderate to high reliability (Cronbach’s alpha = 0.51 to 0.86)
[36,37] (Table 
2).

**Table 2 T2:** Description of primary outcome scales

**Outcome**	**Scale**	**Description**
Self-efficacy	Modified Grossman Self-efficacy for Diabetes Scale [36,37]	The scale contains 25 items that measure the intensity of self-efficacy for activities of the diabetes regimen. Subjects are asked to describe how much they believe they could or could not do what was stated. The responses on this 6-point scale range from “*very sure I can’t*” to “*very sure I can*” do what was stated in each item. Higher scores indicate greater confidence in one’s ability to perform the designated treatment activities. The following statements are examples of the self-efficacy items: “Figure meals and snacks at home” and “Keep track of blood sugar levels”. The modified self-efficacy scale has a moderate to high reliability (Cronbach’s alpha = 0.51 to 0.86).
Self-care behavior	Summary of Diabetes Self-Care Activities Measure – Revised [38,39]	Items selected from this self-report instrument assess participants’ frequency (over the past 7 days) of engaging in diabetes self-care behaviors, including following a healthy diet, spacing out carbohydrates evenly across the day, physical activity, self-monitoring of blood glucose testing, foot care, and medication and/or insulin taking. For each diabetes self-care behavior, participants are asked to respond using the following prompt: “*On how many of the last 7 days*…” Responses, which are based on a 7-day week, range from 0 days to 7 days. Greater number of days indicated better self-management. Reliability and validity for this instrument have been found to be adequate, with a test-retest correlation of 0.40 and internal consistency of 0.47.

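### All secondary-outcome models adjust for self-efficacy without restricting it to the pre-implementation value, so they may not estimate the total effect of the website

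*Protocol article*

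**What the plan says.** All references are to the protocol article, Methods; all but Phase 1 are within Phase 5.

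- **Data analysis, scope:** "Similar modeling will be used for the other outcomes of self-care and quality of life as well as A1C, systolic BP, diastolic BP, LDL and" (the last item on the list is body weight).
- **Data analysis, covariates:** "Each model in the secondary analysis will examine the effect of the intervention while adjusting for self-efficacy, income and ethnicity". Age is added for blood pressure and LDL, and insulin use for weight.
- **Data analysis, reason for the shorter list:** "For secondary outcomes, due to the data being collected less frequently, fewer variables will be included in the model". No reason is given for putting self-efficacy on it.
- **Data analysis, interactions:** "Should the data support it these variables will also be examined as interaction terms with the intervention". Self-efficacy is among these variables.
- **Data analysis, purpose:** "This analysis approach will allow us to examine the effect of the intervention on each of the primary and secondary outcomes". No direct-effect or mediation estimand is named.
- **Primary outcome:** "The primary outcome, self efficacy, will be assessed with the Modified Grossman Self-efficacy for Diabetes Scale".
- **Secondary outcomes:** "self-efficacy was chosen in order to better understand the mediating variables of knowledge use".
- **Phase 1, Intervention development:** "We integrated these interventions with the theoretical framework of self-efficacy".
- **Timing:** Under Participants, the self-efficacy score is among the variables obtained at baseline. Under Data collection, questionnaire data follow every three weeks for nine months before and nine months after launch, 12 points each. Under Secondary outcomes, HbA1c, blood pressure, LDL-C and weight are collected every 3 months.

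**The concern.** The protocol describes a chain: the website raises self-efficacy, and self-efficacy improves self-care and clinical control. A model that holds self-efficacy fixed at each occasion blocks that chain. Its intervention coefficient then answers a different question: what the website does at an unchanged level of self-efficacy. Even that needs self-efficacy and the outcome to have no uncontrolled common cause, such as a change in mood, in other illness or in clinic contact.

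The more the website works as its theory predicts, the less of its secondary benefit such a model would show. The clinical outcomes were chosen to inform the sample size of later trials, so an estimate with part of the effect removed would carry over into their planning. The optional interaction has the same difficulty, because post-launch self-efficacy is itself affected by the intervention and is not a clean effect modifier.

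**Working it through.** **Inputs from the protocol**
- Target change in self-efficacy: 0.5 units. Sample size: at most 52 before the dropout adjustment (Sample size calculation).
- Occasions: 12 before and 12 after for questionnaires. For 3-monthly measures, 9/3 = 3 before and about 3 after.
- Cronbach's alpha of the self-efficacy scale: 0.51 to 0.86 (Primary outcome).

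**Assumptions, not in the protocol**
- Slope of the outcome on self-efficacy within a person, b = 0.4.
- For self-efficacy, and for the part of the outcome it does not explain, variance 1, half between and half within persons.
- Alpha read as reliability, with errors independent across occasions.

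**Step 1. The plan's own figure.** For paired means with SD = 1 (the article gives no SD) and correlation 0.2, n = 2(1 − 0.2)(1.960 + 0.842)² / 0.5² = 50.2, so 51. The exact t calculation gives 53. The stated 52 lies between, so 52 patients and SD near 1 are reasonable working values. This point does not dispute that figure.

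**Step 2. What the adjustment removes.** Let a be the effect of the website on self-efficacy, b the slope of the outcome on self-efficacy, and c the effect by other routes.
- Total effect = c + a·b.
- Coefficient after adjusting for an error-free concurrent score = c.
- With a = 0.5, b = 0.4, c = 0: the total is 0.20 and the adjusted coefficient is 0.00.

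**Step 3. Measurement error.** If the score has reliability R, its error variance is 1/R − 1. The slope is attenuated by λ = 0.5 / (0.5 + 1/R − 1), and the adjusted coefficient is c + a·b·(1 − λ).

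| R | λ | Adjusted coefficient (true total 0.20) |
|---|---|---|
| 1.00 | 1.00 | 0.00 |
| 0.86 | 0.75 | 0.05 |
| 0.70 | 0.54 | 0.09 |
| 0.51 | 0.34 | 0.13 |

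Simulation (2,000 data sets per row, 12+12 occasions, step plus linear time, within-person estimator) gives 0.003, 0.050, 0.095 and 0.134.

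**Step 4. Power for the 0.20 effect.** The unadjusted residual within-person variance is 0.5 + 0.4² × 0.5 = 0.58. The sum of squares of the step term, after removing linear time, sets the standard error.
- 12+12: 6 − 72²/1150 = 1.492 per person; SE = √(0.58 / (52 × 1.492)) = 0.086; power about 64%. Simulation gives 65%, falling to 5% with an error-free concurrent score.
- 3+3: 1.5 − 4.5²/17.5 = 0.343 per person; SE = √(0.58 / (52 × 0.343)) = 0.180; power about 20% (simulation about 19%). The bias is as in Step 3, but there is little power to lose.

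**Step 5. Partial mediation and confounding.** This is a separate simulation: random-intercept model, 52 patients, 3+3 occasions, no time term, error-free score, true total effect 0.30, 100 data sets per case.

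| Share through self-efficacy | Unadjusted | Adjusted for concurrent score | Adjusted for baseline only |
|---|---|---|---|
| 100% | 0.32 | 0.02 | 0.32 |
| 67% | 0.30 | 0.10 | 0.30 |
| 33% | 0.30 | 0.20 | 0.30 |
| 0% | 0.30 | 0.30 | 0.30 |

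Adding an unmeasured time-varying common cause to the 67% case moves the concurrent-score estimate to −0.05, although the true direct effect is 0.10.

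**The case against.** The strongest reply is that the baseline score was meant. Self-efficacy is listed with the baseline variables. The other secondary-model covariates are patient characteristics. For the primary model, the article explains interactions as showing whether the impact differs across levels of a variable, which is the language of effect modification and normally uses pre-intervention values. On that reading nothing is removed, as the last column of Step 5 shows. The reading is possible, so a reader should not infer that the plan certainly strips out the effect. But the model sentence does not say baseline, the score is collected throughout, and the model is a repeated-measures one. The text as written permits the damaging analysis.

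Three further points stand:
- A reader might infer that a fully mediated benefit would be reported as no effect. That is the error-free extreme; at the article's own reliability range, part of the effect remains.
- A reader might infer that bias is always toward zero. That needs direct and mediated effects of the same sign and no common causes; the confounded case changed sign.
- A fall in power from 65% to 5% cannot be carried over to the 3-monthly clinical outcomes, where unadjusted power for the same effect is only about 19%.

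The article also says descriptive analysis will help decide which variables suit as covariates, so the list may not be wholly fixed. That does not remove the need to settle this one, because its unsuitability comes from its place in the causal chain and no distributional check would reveal it.

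**Conclusion.** The point holds as a specification that should be corrected. The protocol adjusts all seven secondary models for a variable that is its primary outcome and intended pathway, without restricting it to a value measured before launch, and presents the result as the effect of the intervention. With the concurrent score, that coefficient is not the total effect, and confounding means it need not be a clean direct effect either.

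The size is a·b times the attenuation factor λ. For the worked case, between 0.07 (at reliability 0.51) and 0.20 (error-free) of a true 0.20 is lost. These figures rest on an assumed slope, variance split and full mediation; the article gives no mediated share, and with none nothing is lost.

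The primary analysis of self-efficacy is untouched, and the collected data allow a correct model. That makes this a should-fix item and not a threat to the study's main conclusion.

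**What to change.** Amend the covariate sentence for the secondary models in one of two ways:
1. Remove self-efficacy from the list; or
2. State that the covariate, and any interaction of it with the intervention, uses only the pre-implementation value.

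Add that any model including post-launch self-efficacy is a separate exploratory mediation analysis, labelled as such, with its no-common-cause assumption stated, and is not reported as the effect of the intervention.

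The cost is a sentence or two of text. No new data, visits or patients are needed, and the stated sample size does not change.
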